#### Medication management

Six consultant psychiatrists will provide medication management. Patients will be accepted into the trial on any medication regimen, with treating psychiatrists using clinical judgment and the Royal Australian and New Zealand College of Psychiatrists clinical practice guidelines for mood disorders to inform medication management decisions [49]. The psychiatrist will see each patient at study entry, and at 6 and 12 months, as well as when requested by the patient’s therapist or the patient.

### Procedure

Patients will enter the study within 3 months of discharge from SMHS. After study entry, individuals will be assigned a psychiatrist for ongoing medication management and a therapist who will deliver IPSRT over 12 months. Baseline assessment will occur within one week of study entry, and will involve SCID-5-RV [44] administered by a research nurse to confirm mood disorder diagnosis and comorbidities, and self-report questionnaires assessing subjective cognitive function (Cognitive Complaints in Bipolar Disorder Rating Assessment, COBRA [50]), psychosocial functioning (Social Adjustment Scale, SAS [51]), depression symptoms (Quick Inventory for Depressive Symptomatology – Self Report, QIDS-SR [52]) and other key factors described below. A research assistant, blinded to randomisation, will conduct objective cognitive assessment (described below) and assess verbal IQ (National Adult Reading Test, NART [53]) in person, as well as measures of longitudinal mood symptoms (Longitudinal Interview Follow-up Evaluation, LIFE [54]), general functioning (Functioning Assessment Short Test, FAST [55]), and medication adherence (Medication Adherence Rating Scale, MARS [56]) via telephone, within one week of baseline assessment. The psychiatrist will complete the clinician-administered versions of the QIDS (QIDS-C [52]) and Young Mania Rating Scale (YMRS [57]) and a clinical research nurse will take blood samples for biological measures.

At 6 months, patients will undergo a second objective cognitive and functional (University of California San Diego Performance Based Skills Assessment, Brief Version (UPSA-B) [58]) assessment (blind research assistant), a telephone interview (same measures as baseline), a psychiatrist review (same measures as baseline), and self-report questionnaires (described below). Immediately following this, patients will be randomised to the group-based CR intervention, or not. The CR intervention will be provided for an 8-week period, commenced between approximately 6 months and 9 months. At treatment-end (12 months) objective cognitive and functional assessment will be repeated, along with all research measures conducted at baseline. Qualitative interviews and treatment satisfaction questionnaires will be completed at 12-months only by a research nurse trained in qualitative methodology. The same measures conducted at the 6-month time-point will be conducted at 18-months (with the exception of the UPSA-B), and at 24 months, three measures will be conducted via telephone (LIFE, FAST, MARS). Schedule of enrolments, assessments and interventions is presented in Table 1 and a populated SPIRIT checklist is provided in Additional file 1.

### Primary outcome

The outcome measures for the trial align with ISBD Targeting Cognition Taskforce recommendations for CR trials in BD [5]. A single composite score (Global Cognition) representing overall cognitive performance at each cognitive assessment (baseline, 6 months, 12 months, 18 months) will be calculated. Change in Global Cognition from 6 months (before randomisation to group-CR) to treatment-end (12 months) will be the primary outcome measure.

Cognitive function will be assessed with a battery of cognitive tasks designed to assess verbal learning and memory, visuospatial learning and memory, sustained attention, working memory, executive functioning, psychomotor speed and social cognition. These cognitive domains are included based on recommendations from the ISBD Targeting Cognition Taskforce [5], as well as research showing these domains to be significantly impaired in acutely-unwell patients with mood disorders [6, 59] and to be sensitive to the effects of Cognitive Remediation interventions [60]. The cognitive assessment will include the following tests:Rey Auditory-Verbal Learning Task [61]Brief Visuospatial Memory Test – Revised [62]Digit Span Forwards and Backwards [63]Trail Making Test – Part A and B [64]Delis-Kaplan Executive Function System—Fluency Battery (Category Fluency, Category Switching) [64]Digit Symbol Coding [63]Continuous Performance Test [62]Stroop Task [64]Negative Affective Priming Task [65]Reading the Mind in the Eyes Test [66]Facial Expression Recognition Test [67]

#### Power

This study is powered on the cognitive outcomes demonstrated in our preliminary RCT of Metacognitive Therapy versus Cognitive Behavioural Therapy for outpatients with MDD [16]. Metacognitive Therapy includes a simple cognitive training intervention (Attention Training Technique). A positive effect size difference between Metacognitive Therapy and Cognitive Behavioural Therapy was found on measures of visuospatial learning and attention (0.6) [16]. To detect a similar effect size for Global Cognition as statistically significant (2-tailed α = 0.05), 45 patients per group would be necessary for 80% power. We aim to recruit 50 patients per group. All statistical tests will utilise a 2-tailed *p*-value of < 0.05 to indicate statistical significance.

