### Factors associated with cognitive impairment and response to cognitive interventions

Factors influencing response to CR are important to identify in order to be able to determine how to tailor interventions to individuals’ cognitive and clinical profiles. This, in turn, should maximise treatment engagement and success. One of the more consistent predictors of CR response is baseline cognitive performance, with poorer performance associated with greater improvement from CR interventions [32]. Less is known about the impact of subjective cognitive difficulties on CR treatment response, but the finding that subjective cognitive difficulties relate to relapse in a large MDD sample receiving antidepressant treatments [33] indicates the importance of investigating this factor further in this context. Several measures of subjective cognitive difficulties, as well as factors likely to be associated with subjective cognitive difficulties (rumination, metacognition, mood severity) are included in the current protocol to determine their impact on CR response in secondary and exploratory analyses. Other factors to be included in exploratory analyses include: childhood trauma, personality traits, circadian rhythm disturbance, and medication adherence (see Methods).

Measurement of key biological processes implicated in mood disorder aetiology and cognitive impairment will occur in this trial, including assessing levels of inflammatory markers (pro-inflammatory cytokines and C-Reactive Protein; CRP) [34–36], vitamin C [37, 38], and androgens (females only) [39]. To be able to comprehensively treat cognitive impairment, the underpinnings of cognitive impairment must be more fully understood; obtaining these biological data will help inform this understanding.

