### Sub-group analyses

Performance on measures at baseline (described above), as well as change in these measures over time, will be used to determine effects on CR treatment response. Additional measures not described above that will be included in sub-group analyses will be the Childhood Trauma Questionnaire (CTQ) [73], the State Trait Anxiety Inventory (STAI) [74], and a Demographic Questionnaire.

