#### Analysis of sub-group effects

Sub-group analyses will use general linear models, and will include sub-group measures and the interaction between treatment arm and these measures. Interaction terms will be used to evaluate the differential effects of CR treatment dependent upon the level of the baseline and change features.

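### The p < 0.05 rule covers about 28 sub-group interactions without limit: with assumed correlations of 0.5 down to 0, about 50% to 76% of trials would show a chance modifier of CR response

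*Protocol article*

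**What the plan says.** The Power section sets one threshold with no exception: "All statistical tests will utilise a 2-tailed *p*-value of < 0.05 to indicate statistical significance".

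The section Sub-group analyses defines the candidate modifiers: "Performance on measures at baseline (described above), as well as change in these measures over time, will be used to determine effects" on response to CR. It adds the childhood trauma questionnaire (CTQ), the anxiety inventory (STAI) and a demographic questionnaire. Analysis of sub-group effects gives the method, general linear models with an arm-by-measure term, and the use: "Interaction terms will be used to evaluate the differential effects of CR treatment dependent upon the level of the baseline and change features". Neither section names a main modifier, limits the number or calls the work exploratory.

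The Background section on factors associated with response gives the purpose, which is to fit treatment to the patient (the quote stops one word short of the sentence's end): "Factors influencing response to CR are important to identify in order to be able to determine how to tailor interventions to individuals’ cognitive and clinical". It describes baseline cognitive performance as one of the more consistent predictors. It places subjective cognition, rumination, metacognition and mood severity in secondary and exploratory analyses. Trauma, personality, circadian disturbance and medication adherence go to exploratory analyses. In the Discussion, Spectrum of mood disorders reports preliminary evidence from the team's previous trial that BD and MDD respond differently to CR, and plans exploratory analyses of this. Screening for cognitive impairment uses the same label for objective and subjective impairment in relation to outcome.

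**The concern.** A 5% threshold limits error for one test. Applied separately to every member of a long, unranked list of interactions, it leaves a substantial chance that something reaches significance when nothing modifies the effect. The sub-group results are meant to guide how CR is tailored to patients, and the abstract lists them. A chance interaction reported as significant could therefore be taken up as a selection rule. The two modifiers with some prior support in the article would have the same standing as all the others.

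**Working it through.** **1. The plan's own figure.** Effect size 0.6, two-sided α = 0.05, 80% power (Power section). Normal approximation: n = 2(1.960 + 0.842)²/0.6² = 43.6, so 44 per group. The two-sample t-test gives 44.6, so 45. This matches the plan ("45 patients per group would be necessary for 80% power"); the sample size is not in question.

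**2. Number of modifiers, one outcome.** Tally from the outcome sections, Sub-group analyses and the Discussion:

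| Group | Measures | Count |
|---|---|---|
| Objective cognition | Global Cognition, six domains | 7 |
| Subjective cognition | COBRA, perceived performance | 2 |
| Functioning | FAST, SAS | 2 |
| Mood | LIFE, QIDS-C, YMRS | 3 |
| Exploratory scales | QIDS-SR, QoL-BD, BRIAN, RRS, MCQ-30, neuroticism, extraversion, MARS | 8 |
| Biological | CRP, one cytokine, vitamin C | 3 |
| Added for sub-groups | CTQ, STAI | 2 |
| Diagnosis | MDD or BD | 1 |
| **Total** | | **28** |

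The tally omits androgens, further cytokines, verbal IQ, demographics and all change versions; counting change roughly doubles it to 56. The assessment timetable (Table 1) is not visible, so availability of all 28 at baseline is an assumption. The text itself places 20 of them at baseline. The other eight are QoL-BD, BRIAN, RRS, MCQ-30, the two personality scores, CTQ and STAI.

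**3. Independent measures.** P(at least one p < 0.05) = 1 − 0.95^k.

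- k = 20: 1 − 0.95^20 = 0.642
- k = 28: 1 − 0.95^28 = 0.762
- k = 56: 1 − 0.95^56 = 0.943

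Expected false positives for k = 28: 28 × 0.05 = 1.4, whatever the correlation.

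**4. Correlated measures.** Simulation of 4,000 null trials with 50 per arm ("We aim to recruit 50 patients per group"). Each modifier had its own linear model with arm, stratum, modifier and arm × modifier, and the interaction was tested at two-sided 0.05. Modifiers were normal and equicorrelated.

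| Average correlation | k = 20 | k = 28 | k = 56 |
|---|---|---|---|
| 0 | 0.65 | 0.76 | 0.94 |
| 0.3 | 0.54 | 0.65 | 0.85 |
| 0.5 | 0.41 | 0.50 | 0.66 |
| 0.6 | 0.35 | 0.41 | 0.55 |
| 0.7 | 0.30 | 0.35 | 0.43 |

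With 28 modifiers in blocks of 4 or 7 (correlation 0.5 to 0.7 within blocks, 0.1 between), the chance was 0.54 to 0.71. A separate simulation with 45 per arm gave 0.77, 0.64 and 0.49 at correlations 0, 0.3 and 0.5.

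**5. What adjustment would do.** In the 45-per-arm simulation, Benjamini-Hochberg at 5% over 28 interactions gave a chance of any false discovery of about 5% at all three correlations. It costs power. Take one true interaction slope of 0.5 SD per SD with 45 per arm and residual SD 1. The standard error is √(1/45 + 1/45) = 0.211, so the expected z is 0.5/0.211 = 2.37. Power is about 65% at 0.05 and about 21% at 0.05/27, which approximates the first Benjamini-Hochberg step. For a slope of 0.4 it falls from about 47% to about 10%.

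**The case against.** The strongest reply is that this work is exploratory and that a condensed article need not give its multiplicity rules. The Background and Discussion do use that label for diagnosis-specific effects, trauma, personality, circadian disturbance, adherence, and objective versus subjective impairment. An analysis plan that is not shown could add a rule. This stands in part: the label would change how a significant interaction is read. It does not change the error rate, the Background also uses the word secondary, and the sections that define the analysis do not carry the label. The point also does not rest on a missing correction. It rests on a stated rule that covers all tests.

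Several stronger readings are tempting and are not supported.

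- A reader might infer that a significant modifier is the expected result under no effect, or that the trial cannot tell a real modifier from chance. At higher correlations or with fewer modifiers the probability is below one half, and a modifier named in advance still faces a 5% error.
- A reader might infer that every p < 0.05 will be declared a predictor of response. The article defines significance and says interactions will evaluate differential effects; it states no such declaration.
- A reader might infer that only baseline cognition has prior support. Diagnosis also has it, from the team's own previous trial, and it is the stratification factor.
- A reader might conclude that a formal adjustment of all interactions is required. Given the power cost in step 5, unadjusted estimates clearly labelled as exploratory are a defensible alternative.

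**Conclusion.** The concern holds as a matter of scope. The unrestricted p < 0.05 rule reaches a family of about 28 interactions per outcome, in which at least one chance finding arises with probability about 76% (independent), 65% (correlation 0.3) or 50% (correlation 0.5), with about 1.4 expected. This assumes that the tallied measures are available at baseline and takes correlations that the article does not give. The probability drops below one half at average correlations of about 0.5 to 0.6 or more for 28 modifiers, and sooner for fewer. Counting change versions raises it. The planned sample size and the primary test are unaffected. What needs correcting is the standing that the written rule gives to sub-group findings, so this is a change that should be made but not a flaw in the main comparison.

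**What to change.** 1. In Power, limit the significance sentence to the primary and secondary treatment comparisons.
2. In the two sub-group sections, name baseline cognitive performance and diagnosis (MDD versus BD) as the pre-specified interactions on the primary outcome. If each is tested at 0.05 and they are independent, the chance of a false finding among the two is 1 − 0.95² = 9.75%; this should be acknowledged.
3. State that all other interactions, baseline or change, are exploratory and hypothesis-generating. Report them with estimates, confidence intervals and the number tested, and claim no modifier from an unadjusted p < 0.05. If such a claim is wanted, a false discovery rate adjustment is one option.

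The cost is a few sentences, with no extra patients, data or assessments. The downside is weaker claims for non-prioritised modifiers, and lower power for them if adjustment is used.

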#### Analysis of primary outcome

Global Cognition will be calculated by averaging *Z*-scores across each cognitive domain, as listed above. A change *z*-score from 6- to 12-month follow-up will then be calculated using the Global Cognition score from these time-points. Change *z*-scores on Global Cognition will be compared using general linear models, with an intention-to-treat (ITT) approach. Treatment arm (IPSRT-CR versus IPSRT) and stratum (MDD versus BD) will be fixed factors, as in Douglas et al. [30].

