### Randomisation

Randomisation to the group-based CR intervention, or not, will occur at 6 months. This time-point has been chosen to avoid differential early dropout based on randomisation and to provide a period of mood stabilising treatment prior to CR treatment. Computerised permuted block randomisation will be undertaken by the team’s biostatistician (CF) prior to the commencement of the study and will be stratified according to mood disorder type (BD or MDD). Sequentially numbered envelopes will be stored in a locked cabinet by an independent research coordinator and given to therapists after the 6-month research assessment. Each patient will be allocated a randomisation number which will not be re-allocated if the patient drops out of the study.

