#### Analysis of secondary and exploratory outcomes

To assess the effect of IPSRT-CR versus IPSRT on secondary and exploratory outcomes, general linear models will be used. These models will use treatment arm (IPSRT-CR versus IPSRT) and stratum (MDD versus BD) as fixed factors. Analyses will adopt an ITT approach.

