### Spectrum of mood disorders

Individuals with MDD or BD will be recruited into the trial to be able to produce a more generalisable sample of relevance to community mental health services in New Zealand. We note, however, that most CR trials in mood disorders to date have recruited either BD or MDD samples. It is possible that having a mixed diagnostic sample may dilute any findings specific to BD or MDD. Indeed, in our previous RCT we found preliminary evidence of BD and MDD groups responding differentially to CR [30]. We plan, therefore, to include diagnosis type (MDD or BD) as a covariate in our analyses, to stratify randomisation according to diagnosis, and to examine effects specific to BD or MDD in exploratory analyses. The ability to conduct head-to-head comparisons between MDD and BD groups with regards to CR treatment response is a strength of this trial. Furthermore, in previous trials the diagnosis has changed during the 12-month intervention period on the basis of careful observation of, for example, mixed states and emergent or previously unrecognised hypomania. Including the spectrum of mood disorders therefore allows for a more considered examination of this spectrum.

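### The primary model fixes the slope on the 6-month Global Cognition score at 1; adding that score as a covariate would gain precision at almost no cost

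*Protocol article*

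**What the plan says.** The Primary outcome section defines the endpoint: "Change in Global Cognition from 6 months (before randomisation to group-CR) to treatment-end (12 months) will be the primary outcome measure". Under Analysis of primary outcome, the change z-"scores on Global Cognition will be compared using general linear models, with an intention-to-treat (ITT) approach", and the model terms are given as "Treatment arm (IPSRT-CR versus IPSRT) and stratum (MDD versus BD) will be fixed factors", following the team's previous trial. No 6-month score is listed. For the other outcomes, Analysis of secondary and exploratory outcomes repeats the specification: "These models will use treatment arm (IPSRT-CR versus IPSRT) and stratum (MDD versus BD) as fixed factors".

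The only covariate named elsewhere is diagnosis. Spectrum of mood disorders states the intention "to include diagnosis type (MDD or BD) as a covariate in our analyses", which is the stratum again. The Randomisation section stratifies by diagnosis and nothing else. Measures taken at baseline enter models only under Analysis of sub-group effects, as interactions with arm.

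The Procedure section places the 6-month cognitive assessment immediately before randomisation. The Power section says of an effect size of 0.6 that, to detect it "as statistically significant (2-tailed α = 0.05), 45 patients per group would be necessary for 80% power", and gives a target of 50 per group.

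**The concern.** A change score subtracts the starting value with a coefficient of exactly 1. If the true slope of the 12-month score on the 6-month score is below 1, two things follow.

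- The outcome keeps variance that the 6-month score could have explained, so the confidence interval is wider than it need be.
- A chance difference at 6 months is over-corrected. The arm that happens to start lower tends to show the larger rise through regression to the mean, and part of that rise is read as treatment effect.

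Stratification by diagnosis does not balance cognition directly, and there are only about 50 patients per arm. The protocol itself expects improvement to depend on starting level: it counts among the more consistent predictors of response "baseline cognitive performance, with poorer performance associated with greater improvement from CR interventions". At stake are some power on the primary comparison and an estimate that moves with whatever imbalance occurs.

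**Working it through.** **Inputs from the article.** Effect size 0.6, two-sided alpha 0.05, 80% power, 45 per group needed, 50 per group planned (Power). Model terms: arm and stratum (Analysis of primary outcome).

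**Assumptions.** The 6-to-12-month correlation r is not given, so 0.5 to 0.9 is shown. Variances at the two times are taken as equal. The 0.6 is read in SD units of the change score; the article does not state the unit.

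**Step 1: reproduce the plan's figure.** A two-sample t-test with d = 0.6 needs 44.59, rounded up to 45 per group (44 by the normal approximation). Power is 80.4% at 45 per group and 84.4% at 50. The plan's figure holds.

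**Step 2: variance with and without the covariate.** With score variance 1:

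- change score: 2(1−r)
- change score adjusted for the 6-month value: 1−r²
- ratio: (1−r²) / [2(1−r)] = (1+r)/2

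**Step 3: power.** The effective effect size is 0.6/√[(1+r)/2]. At r = 0.7 this is 0.6/√0.85 = 0.651.

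| r | Variance ratio | Per group for 80% power | Power at 45 | Power at 50 | Narrower interval |
|---|---|---|---|---|---|
| planned model | 1 | 45 | 80.4% | 84.4% | – |
| 0.5 | 0.75 | 34 | 90.2% | 92.9% | 13.4% |
| 0.7 | 0.85 | 39 | 86.3% | 89.7% | 7.8% |
| 0.8 | 0.90 | 41 | 84.3% | 87.9% | 5.1% |
| 0.9 | 0.95 | 43 | 82.3% | 86.2% | 2.5% |

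Out of 100 patients, the planned model gives up information worth about 25, 15, 10 or 5 at these four values of r.

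**Step 4: chance imbalance.** One standard error of the 6-month difference at 50 per arm is √(2/50) = 0.2 score SD. Given such an imbalance, the change-score estimate shifts by −(1−r) × 0.2: −0.10, −0.06, −0.04 and −0.02 score SD at r = 0.5, 0.7, 0.8 and 0.9.

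**Step 5: simulation check** (4,000 trials for each r, 50 per arm, arm and stratum in both models). The slope of the estimate on the 6-month imbalance was −0.50, −0.31, −0.21 and −0.10 without the covariate and about 0 with it. Both models were unbiased on average over randomisations.

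**Step 6: the missing-data rule.** The Missing data section assumes zero change where data are incomplete. If a fraction m of patients, missing at random with respect to the scores, is set to zero change, the ratio becomes 1 − (1−m)(1−r)/2. For an assumed m = 20%, that is 1 − 0.8 × 0.15 = 0.88 at r = 0.7 and 1 − 0.8 × 0.10 = 0.92 at r = 0.8, against 0.85 and 0.90 with complete data. The gain shrinks somewhat but remains.

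**The case against.** A reader might infer that the model ignores the 6-month score, leaves imbalance uncorrected, or gives a biased result. The documents do not support this. The score is in the outcome with a fixed coefficient, imbalance is over-corrected rather than left alone, and a change-score model with the stratification factor is a legitimate analysis. Nor is the sample size wrong.

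The size of the gain is also open to challenge:

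- If r is high, as one may assume for a composite of many tests, the gain is small. At r = 0.9, power at 50 per group moves only from 84.4% to 86.2%.
- If 0.6 is in SD units of the score itself, power is already high when r is 0.7 or more. At 45 per group it goes from 95.3% to 97.6% (r = 0.7) or from 99.4% to 99.7% (r = 0.8). The variance ratio is unchanged, but little power is left to gain.

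The protocol's remark on starting cognition concerns response to cognitive remediation. That is chiefly effect modification, which the sub-group models address. It is not direct evidence that starting level predicts change in both arms. The case for the covariate does not need it: any r below 1 suffices under equal variances.

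Finally, a list of fixed factors in a condensed article need not exclude a continuous covariate. This is weak, because diagnosis is the only covariate that the article names for its main analyses.

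These points limit the size and seriousness of the matter. None is a reason to leave the score out.

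**Conclusion.** The point holds as a matter of efficiency. As written, the primary model is valid and unbiased over randomisations, but it is less precise than the same model with the 6-month score, and its estimate is biased conditional on a chance imbalance at 6 months. The variance saving is 25% at r = 0.5, falling to 5% at r = 0.9. In power at 50 per group, that is a gain of 8.5 points (92.9 − 84.4) down to 1.8 points (86.2 − 84.4). These figures rest on equal variances, on 0.6 in change-score SD units, on complete data, and on an r that the article does not give. This is a recommended improvement at negligible cost; the documents do not support calling it an error that must be corrected before the trial can be trusted.

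**What to change.** In Analysis of primary outcome, prespecify the 6-month Global Cognition score as a continuous covariate beside arm and stratum. The arm contrast is still the difference in 6-to-12-month change; with that covariate, modelling change or the 12-month score gives the same treatment estimate.

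In Analysis of secondary and exploratory outcomes, add each outcome's own last pre-randomisation value where one is measured: the 6-month value, otherwise the study-entry value. The qualification matters because the Procedure section describes blood sampling at baseline and does not mention it among the 6-month assessments, so a 6-month value cannot be confirmed for every outcome.

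The cost is a sentence of wording in each section and one degree of freedom per model. For the primary outcome the score is already scheduled. The change should be fixed before unblinding, since adding the covariate after an imbalance has been seen would be open to challenge. It does not settle whether assuming zero change for missing data is appropriate, which is a separate question.
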